#### Secondary outcome measures

The secondary outcome of this study is the impact of stroke diagnosis on ADL involving the use of the upper limb. We use the Fugl-Meyer Assessment for Upper Limb (UE-FM), Barthel Index, and the Stroke Impact Scale to quantify these variables.

For the interaction with the RGS system, we measure the daily use, derived estimates of joint synergies, range of motion, reaching speed, precision, etc. (see [17] for details on the analyzed parameters). For the RGSwear, we analyze the daily use based on step count and accelerometer data.

### Intervention and control groups

As explained in the “Allocation and blinding” section, patients are allocated in a randomized fashion either to the intervention group (RGS treatment plus rehabilitation as usual) or to the control group (standard care) (see Fig. 3 and Tables 2 and 3).

The *intervention group* follows a rehabilitation program for motor training using the RGS system at the clinic and home in addition to standard care. The training consists of various RGS-based exercises involving reaching, grasping, and placing virtual objects in a virtual environment. The training period and the number of training sessions are variable. They are set by the treating clinicians based on the patients’ needs and on dosage guidelines agreed by the three clinical partners in the trial (see the “Treatment dosage” section). Patients recruited at the subacute phase (inpatients) will receive the rehabilitation treatment via RGS at the hospital, from recruitment until discharge. In addition, the patients in the intervention group are prescribed occupational or physical therapy following the local clinical practice of the rehabilitation unit from admission to discharge. Patients recruited after discharge (outpatients) will train with RGS at their homes daily for 3 months, including weekends. All the patients in the intervention group (inpatient and outpatient) receive the RGSwear at recruitment for up to 1 year post-recruitment.

The *control group* receives standard care provided to patients after clinical discharge, which varies according to the patients’ condition and the different standards of care practiced in each EU country [18]. Also, at discharge, patients are provided advice for continuing voluntary rehabilitation in their homes. Given the huge regional variability, a detailed description of standard care is not reported in this study. In the footnote, we have provided the links to the National Health guidelines for Spain^1^, France^2^, and Sweden^3^.

### RGS protocols and training

The clinicians at each hospital have access to the RGS Medical Information Management System (MIMS), where they can select the training protocols and schedule the exercises for each patient. Training includes motor exercises for the upper limbs and hands such as reach, grasp, release, finger flexion, and pronation/supination. The exercises are combined with cognitive components (see Fig. 4). A variety of gamified exercises is proposed to ensure adherence to the treatment. The patients observe their movement performed by the virtual arms from a first-person perspective in a VR environment while performing the exercises in a horizontal (arms on the table) or vertical (arms up in the air) space. The patients’ movements (kinematics) and performance (gamified exercises) are recorded and stored in a secure remote database for future analysis (see the “Data collection and management” section).

**Fig. 4 Fig4:**
[figure not shown]
RGS training exercises*.* Examples of gamified exercises for the upper limbs with horizontal movement (spheroids, clean the table, pinball, hockey) or vertical movements (constellations, grab, and place) and exercises for the hands (bubbles, demolition)

### Treatment dosage

The RGS@home group follows a standardized intervention schedule as follows:Daily training, including weekends.Recommended training time is 24–28 min per day.The number of exercises per day is between four and nine.The duration of each exercise should be about 6 min.At least one exercise should be changed every 2 weeks.Patients are free to train more than prescribed.

After finishing the daily sessions prescribed by the therapists, patients are allowed to continue using the RGS protocols and repeat as many exercises as they want during the rest of the day. In addition, the RGSwear reminds the patient every other day to perform a task to move the paretic arm called circle drawing. We aim to correlate this movement with the Fugl Meyer Scale. This task consists of making several horizontal and vertical circles (clockwise and anticlockwise) on a table (without gravity) then the same task vertically in a non-obstructed space against gravity (see Fig. 1).

### Adherence to treatment

It is a common problem that patients sometimes lack the motivation to follow their training program when there is no direct supervision [19]. With RGS@home and RGSwear, the patient is continuously monitored, and the clinicians can detect low adherence and contact the patients. To further improve adherence, the exercises of the RGS-based training are designed to include gamification and motivational factors to avoid monotonous training. In addition, the AI component of RGS adapts the exercises to the patient’s abilities (increases or decreases the difficulty), thus avoiding frustration or boredom and facilitating patients’ adherence. Patients are free to leave the study at any time and will not be included in the study if they stop using RGS@home for more than five consecutive days. Patients are also free to participate in leisure activities. However, they should not participate in other clinical trials investigating rehabilitation approaches or technologies.

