**Fig. 2 Fig2:**
[figure not shown]
The RGS platform and its use during the patient’s journey to recovery. The RGS grants a continuum of care and rehabilitation, monitoring, and analytics that supports clinicians in their decision-making (Medical Information Management System (MIMS)) and stroke patients (inpatients and outpatients) and with a “soft-landing” from the hospital to home

RGS@home is a multicentric study, and the trial is conducted in three different hospitals across Europe, namely, Spain, Sweden, and France. Thus, this study will also provide insights into whether the proposed system can be used independently of country-specific practice, standards of stroke care, and reimbursement systems. We hypothesize that the RGS setup combined with conventional therapy will be a more effective rehabilitation program than conventional therapy alone. More specifically, we expect the combined approach to show high adherence to treatment and higher effects on function and well-being, while costs will be reduced. A specific effect we seek to reveal is the positive feedback between rehabilitation, ADLs, and recovery, which we see as a process that can overcome deterioration which can be achieved with e-health solutions. We hypothesize that spontaneous use of the paretic limb, as measured with the RGSwear wearable, is predictive of recovery.

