### Allocation and blinding

After being assessed for eligibility, patients are randomly allocated to either the intervention or control group (allocation ratio 2:1). The larger sample size in the experimental group allows more variables to be tested and gives more power to detect relevant effects in the experimental intervention. Randomization is realized via an adaptive stratified sampling (i.e., minimization) through the computerized encrypted cloud-based database (electronic case report form (eCRF)), which takes into account three conditions to balance the two groups: (1) time since stroke (≥ 30 days), (2) age (≥ 20 years old), and (3) severity (≥ 2 MRC). The allocation is concealed while patients and clinicians (except those involved in the baseline assessment) are not blind to the group allocation. A sham group was excluded from the design because an earlier study has shown a superior rehabilitation effect of training with RGS over sham computer game training using the Wii gaming console [10]. Since this is a first-of-a-kind study evaluating the outcomes (see Tables 2 and 3.) of an AI platform for rehabilitation, the sample size has been determined by feasibility (3 years) and estimated by considering the monthly number of eligible inpatients and outpatients of the participating hospitals. We plan to include a total of 90 patients via the clinical partners in the consortium. Each hospital will be recruiting 30 patients, 20 in the intervention group and 10 in the control group.

**Table 2 Tab2:** Study procedure and assessment

Study procedure	Screening and baseline assessment		Control group, standard care	Intervention group, 0–3 months daily sessions of 24 min or more	Post-treatment assessment		
	Inpatients	Outpatients			3 months	6 months	12 months
Informed consent	x	x					
Medical history	Patients’ demographics MRI/CT scan when available						
Assessment: domains and scales							
Disability and impairment	Barthel Index (BI)				x	x	x
	Stroke Impact Scale (SIS)				x		x
	Fugl-Meyer Assessment of the upper limb (UE-FM)				x	x	x
	Chedoke Arm and Hand Activity Inventory (CAHAI)				x		x
	Hamilton Depression Rating Scale (HDRS)				x		x
	Visual analog score (VAS) for pain				x		x^a^
	Modified Ashworth Scale (AS) for spasticity				x^a^		x
	Fatigue Severity Scale (FSS)				x		x
	Grip force^a^				x^a^		x^a^
	Kinematics from the motion capture camera of the RGS@home system				x	x	x
	RGSwear data (paretic arm)				Continuous		
	Incidents related to use				x		x

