**Fig. 3 Fig3:**
[figure not shown]
Clinical trial timeline. Participants are recruited as inpatients shortly after a stroke or as outpatients after hospital discharge. After a pre-selection, participants receive baseline evaluations and are randomly assigned to the intervention group or control group. The inpatients start using the RGS desktop setup during their stay at the hospital, while the outpatients use RGS directly in their homes. All participants in the intervention group are provided with a wearable device (RGSwear) for continuous monitoring. The control group receives rehabilitation as usual according to the standard care of the countries included in the study. According to the outcome measures assessments, all participants are evaluated again at 3, 6, and 12 months after baseline evaluation (see Tables 2 and 3)

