## Statistical method

We will perform mainly between-subject analysis by comparing the mean outcomes of the experimental group with the mean outcomes of the control group. To analyze the clinical outcomes related to disability and impairment, we will calculate the normalized improvement, which shows improvement or decline in proportion to the maximum score possible in the respective scale, therefore avoiding ceiling effects. Depending on whether the data is following a normal distribution, we will use parametric or non-parametric statistics. In the case of non-normal data, medians will be reported. We will perform an intention-to-treat analysis. The last observation carried forward analysis will be performed alongside a complete-case analysis to account for missing data.

To address the *primary outcome on disability and impairment*, a between-subject analysis will be used to compare the change in disability (Barthel Index (BI)) between the experimental and control groups at baselines 3, 6, and 12 months.

For the *secondary outcomes* on usability and impairment and other planned comparisons, we will perform the following analysis (for abbreviations, see Table 2):

Changes in independence (CAHAI), participation (SIS), depression (HDRS) fatigue (FSS), pain (VAS), spasticity (mAS), and impairment (BI and FM-UE) are analyzed from baseline to months 3 and 12.

We will also look at the change in grip force and correlate it with FM-UE, CAHAI, and BI from baseline to 3 months and 12 months. The outcomes of this measure are important to evaluate the clinical effectiveness of the RGS intervention to reduce disability and impairment. To measure quality of life, we compare the group changes in the quality of life (SSQOL) and well-being (SF-36) from baseline to 3 months and 12 months. We will also compare well-being (SF-36) at 6 months.

For the additional variables shown in Table 3, we will proceed as follows:

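### Removing patients who stop RGS@home for more than five days can affect only the intervention arm and conflicts with the planned intention-to-treat analysis

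*Protocol article*

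**What the plan says.** All places are in the protocol article.

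- **Adherence to treatment:** patients may leave at any time and "will not be included in the study if they stop using RGS@home for more than five consecutive days".
- **Intervention and control groups:** the two arms are described as ("RGS treatment plus rehabilitation as usual) or to the control group (standard care"). The Fig. 3 legend agrees: "The control group receives rehabilitation as usual according to the standard care of the countries included in the study". It also places RGS use after baseline evaluation and random assignment.
- **Allocation and blinding:** patients are "randomly allocated to either the intervention or control group (allocation ratio 2:1"), and "We plan to include a total of 90 patients via the clinical partners in the consortium", with 20 intervention and 10 control patients at each of three hospitals.
- **Statistical method:** "We will perform an intention-to-treat analysis". On missing data: "The last observation carried forward analysis will be performed alongside a complete-case analysis to account for missing data".
- **Primary outcome measures:** the amount of use at home is the fifth of five domains in the compound score.
- **Study rationale and hypotheses:** "we expect the combined approach to show high adherence to treatment".

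No adherence rule is given for controls. Nothing says whether a patient who stops RGS is still assessed at 3, 6 and 12 months, or stays in the analysis set.

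**The concern.** A control patient has no RGS to stop using, so the rule can remove patients from the RGS arm only. It acts after randomisation and depends on behaviour under the assigned treatment. Intention-to-treat analysis is meant to prevent selection of that kind, and the article promises such an analysis without saying how the two statements fit together.

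Two results are at stake. The first is the between-arm comparison on the Barthel Index, quality of life and readmission, because the RGS patients who remain would no longer be comparable with the controls. The second is the acceptability result. The rule selects on home use, which is itself part of the primary compound score and bears on the hypothesis of high adherence. Mean use among those who remain can therefore be raised by the rule itself.

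**Working it through.** **1. Planned numbers.** 3 hospitals × 20 = 60 RGS patients and 3 × 10 = 30 controls. The total is 90 at 2:1, which reproduces the article's figure. The sample size rests on feasibility, so there is no power statement to reproduce. The rule can act on the 60 and never on the 30.

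**2. Could it be an entry criterion?** No. Stopping use presupposes that use has begun, and RGS is supplied only after allocation. The rule is also absent from the eligibility table (Table 1). Two readings remain: deletion from the analysis, or end of participation with data kept.

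**3. Reading A: deletion, or loss from the complete-case analysis.** The article gives no removal rate and no link between adherence and outcome, so these inputs are assumptions:
- p = share of the RGS arm removed
- d = how much worse the removed patients do than those kept, in SD units
- no true treatment effect, unit SD, two-sided 5% test

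Bias = p × d. SE = √(1/[60(1−p)] + 1/30). The rejection rate is the chance that a normal variable with mean bias/SE and unit variance falls outside ±1.96.

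| p | d | RGS patients left | Bias (SD) | SE | Rejection rate |
|---|---|---|---|---|---|
| 0.05 | 0.5 | 57 | 0.025 | 0.226 | 5.1% |
| 0.10 | 0.8 | 54 | 0.08 | 0.228 | 6.4% |
| 0.20 | 0.5 | 48 | 0.10 | 0.233 | 7.1% |
| 0.30 | 0.8 | 42 | 0.24 | 0.239 | 17.1% |
| 0.40 | 0.8 | 36 | 0.32 | 0.247 | 25.3% |

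A second model was simulated (20,000 trials per scenario, t-test). It removes the lowest-adhering fraction f of the RGS arm, with correlation ρ between adherence and outcome. The bias is ρ·φ(z_f)/(1−f), where z_f is the normal quantile at f.
- f = 10–30% and ρ = 0.3–0.5: bias about 0.06–0.25 SD, rejection rate about 5.5–19%.
- ρ = 0: no bias, rejection rate about 5%.
- All 60 + 30 patients kept and followed: 4.6–5.2% in every scenario.

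**4. Reading B: participation ends, data kept, last observation carried forward.** Take a patient who stops before month 3. Baseline is carried forward, so the change is zero. Let m be the mean improvement in both arms (assumed). The kept patients average m + pd, so the RGS arm averages (1−p)(m + pd) and the bias is (1−p)(m + pd) − m.
- p = 0.4, d = 0.8, m = 0.3: 0.6 × 0.62 − 0.3 = +0.07 SD
- p = 0.2, d = 0.5, m = 0.3: 0.8 × 0.40 − 0.3 = +0.02 SD
- p = 0.2, d = 0.5, m = 1.0: 0.8 × 1.10 − 1.0 = −0.12 SD
- p = 0.4, d = 0.5, m = 1.0: 0.6 × 1.20 − 1.0 = −0.28 SD

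The sign depends on how much patients improve in general. The complete-case analysis planned alongside would still lose these patients at visits not made, which returns to Reading A.

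**5. How often would the rule be met?** Suppose each day in a 90-day period is skipped independently with probability q. A run of six or more missed days then occurs in 0.01%, 0.4%, 4.3%, 19.3% and 50.7% of patients for q = 0.1, 0.2, 0.3, 0.4 and 0.5. Independence is a weak model for someone who stops altogether, so this shows only that the rate could be negligible or large.

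**The case against.** The strongest reply is that the wording need not mean deletion. The clause stands in the same sentence as the right to leave the study, so it may describe the end of participation. The intention-to-treat commitment and the carried-forward analysis would then keep the patient in the RGS arm. This stands as far as it goes: a reader might infer that the rule must favour RGS in every analysis, and the documents do not support that. Patients who have recovered well might also stop, and no passage says that stoppers do worse. But this reading does not restore the randomised comparison, because outcome collection would still end early in one arm only.

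A reader might also infer that the rule is easily triggered and that many patients will be lost. The documents do not support that either. The Discussion informally reports use above the prescribed amount, and under independent skipping the rule is rarely met at daily skip probabilities up to 0.3.

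Nor do low users vanish from the report. The number and reasons of dropouts are a listed assessment (Table 2), dropouts are tracked in both groups (Statistical method, Acceptance), and reasons are analysed (Harms). That limits the acceptability concern but does not remove it, since mean use among those remaining can still be inflated. Finally, no passage says that anyone has already been removed.

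**Conclusion.** The conflict is established from the text alone and needs no assumed figure. The article states a one-arm, post-randomisation removal on adherence beside an intention-to-treat commitment, and the rule selects on a component of the primary compound score. This is a contradiction between two stated rules, not a detail left to a fuller document.

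The size and direction of the bias are conditional. If patients are deleted and stoppers do worse, the bias is toward RGS: about 0.03–0.32 SD, with a rejection rate of about 5–25% under no true effect, for assumed removal of 5–40% and a deficit of 0.5–0.8 SD. At 5–10% removed, the inflation is slight (5.1–6.4%). If adherence is unrelated to outcome, there is none. If participation ends and the last observation is carried forward, the bias ran from about +0.07 to −0.28 SD for p = 0.2–0.4, d = 0.5–0.8 and m = 0.3–1.0 SD. The actual removal rate is unknown.

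**What to change.** Reconcile the Adherence to treatment and Statistical method sections by replacing the removal clause with wording such as: *A patient who stops using RGS@home for more than five consecutive days is recorded as non-adherent, remains in the trial, is assessed at 3, 6 and 12 months where consent allows, and is analysed in the arm to which the patient was randomised.*

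Report home use over all patients randomised to RGS. Any analysis restricted to or adjusted for adherence should be a labelled secondary analysis. If any patients have already been removed, seek their follow-up where consent allows.

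This concerns follow-up and analysis only and takes no position on when RGS use itself should stop. The cost is one changed clause and the assessment visits for patients who stop. The estimated effect and mean use may be less favourable to RGS as a result.

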## Data collection and management

The clinical outcome measurements and the patients’ data are collected by each participating hospital by blinded clinicians and logged in the eCRF. Data obtained through the interaction with the RGS ecosystem is automatically logged in the MIMS. The data in the eCRF is securely stored and anonymized (patients are assigned an ID), and monitoring is organized by each clinical partner independently, adhering to local standards and procedures. To ensure all data is logged correctly and no duplicates exist, the RGS@home eCRF process automatically checks to ensure that the logged scores of the clinical scales and tests are valid. Two workshops have been organized with the study coordinators to understand how the assessments are performed and the data collected.

The data obtained from the interaction with the RGS ecosystem (kinematic data, prescriptions, protocol events, and use) is automatically stored in the MIMS, a secured cloud-based database that the participating hospitals can access via a web browser with a username and password. Within the MIMS, and separately from the eCRF, the participating hospitals can create profiles (anonymized) for each patient, determine and manage the prescriptions of exercises, and track the patient’s progress through dashboards, graphics, and analytic reports. The sponsor can remotely access the password-protected data in the MIMS to analyze the interaction with the RGS system.

### Data monitoring

The eCRF is provided by an external Contract Research Organization or CRO (SAIL, Barcelona) independently of the study sponsor. The CRO provides technical support and ensures that the data is safely stored on a secured server protected against unauthorized access. The CRO ensures that the eCRF was created according to the project’s needs by including mechanisms that ensure that the data is logged correctly (i.e., cannot exceed the scores’ max values), ranges are provided, or additional fields are provided to add information that ensures proper recording and understanding). Each clinical partner has access to the eCRF to enter the data collected and is responsible for correctly logging the data collected from their patients and ensuring the monitoring and auditing of that data. Harmonization workshops have been organized to ensure that data is assessed homogeneously across the clinical partners.

The CRO agrees that data can be extracted from the eCRF by the sponsor four times a year to perform preliminary analyses and comply with the trial’s reporting requirements. The anonymized data is shared only between the sponsor and the analytics partner responsible for data analysis.

